## Abstract

**Background::**

Fracture is a common disease; many factors affect fracture healing. Recent studies have confirmed that hydrogen sulfide (H_2_S) plays an essential role in bone formation, but most of these studies are drawing conclusions based on animal experiment; whether H_2_S could promote fracture healing in patients is still unclear. We aim to investigate the change of serum H_2_S in fracture patients, and analyze its effort on fracture healing.

**Methods::**

This is a single-center, prospective cohort study. Patients with spinal or limb fracture will be recruited. Patient's serum and urine will be collected at baseline for examination (serum H_2_S, β-CTX, OC, PINP, 25-OH-VitD_3_, S-CTX, urinary calcium, and urinary creatinine). All patients will be followed-up for 24 months in outpatients settings, the image of X-ray or CT will be reviewed and fracture healing will be judged by 2 experienced orthopedic physicians. The difference in serum parameters especially H_2_S will be compared between patients with fracture healed within 9 months and those with fracture unhealed at 9 months.

**Discussion::**

Results of the trial could provide insight into influence of H_2_S on fracture healing.

**Ethics and dissemination::**

The study was approved by the ethics committee of School of Medicine UESTC & Sichuan Provincial People's Hospital Ethics Committee. All the participants will be asked to provide written informed consent before data collection. The findings of the study will be published in peer-reviewed journals and will be presented at national or international conferences.

## Introduction

1

Fracture is common in clinical practice, healing without deformity and restoring limb function as soon as possible is the goal of fracture treatment. To date, the detailed pathophysiological mechanism of fracture healing has not been fully clarified. Previous research elucidated that the process mainly depends on the action of osteoblasts and osteoclasts, and is regulated by many cytokines, such as bone morphogenetic protein-2 (BMP-2), transforming growth factor β (TGF-β) and fibroblast growth factor (FGF).^[1,2]^

Hydrogen sulfide (H_2_S) is a gastrotransmitter and plays important regulatory roles in cardiovascular, gastrointestinal, and neurological diseases.^[3,4]^ Cystathionine b synthase (CBS), cystathionine c lyase (CSE) or 3-mercaptopyruvate sulfurtransferase are key enzymes generating H_2_S as L-cysteine as a substrate.^[5]^ In recent years, many studies have confirmed H_2_S plays an essential role in bone metabolism. H_2_S decreases osteoclast differentiation induced by nicotine or lipopolysaccharide^[6]^ and osteoclast progenitor differentiation,^[7]^ which decreases necrotic bone absorption during bone healing, but benefits osteoporosis. As well, H_2_S decreases matrix metalloproteinase activity in bone matrix,^[8]^ thereby accelerating matrix mineralization. Finally, H_2_S promotes bone marrow mesenchymal stem cells mineralization by Wnt signals.^[9]^ and reduces MC3T3-E1 preosteoblast cell injury induced by H_2_O_2._^[10]^ Our work found that CSE-H_2_S sulfhydrated Runt-related transcript factor 2 (RUNX2) enhanced its transactivation and increased osteoblast differentiation and maturation, thereby promoting rat bone healing.^[11]^ However, the above studies are based on animals or cultured cells, whether H_2_S plays similar role in patients with fracture is still unclear.

In this study, we aimed to investigate the change of serum H_2_S in fracture patients, and analyze its effort on fracture healing.

## Methods and analysis

2

### Study design

2.1

This is a single center, prospective, cohort study at the Sichuan Provincial People's Hospital, which is a referral hospital for trauma and has case volume necessary for the study. Trial is registered at Chinese Clinical Trial Registry (ChiCTR1900026045). This study included fracture group and control group, and is a 24-month study, which started in July 2019 and will be ended in June 2021.

The primary outcome is concentrations of serum H_2_S. The secondary outcomes are bone turnover markers^[12,13]^ (including serum β-C-terminal telopeptide of type I collagen (β-CTX), procollagen type I N-terminal propeptide (PINP), osteocalcin (OC), serum C- terminal telopeptide of type I collagen (S-CTX),25-OH-VitD_3_ and urinary calcium/creatinine) and time between surgery and healing of the fracture. These indexes will be measured at specific time points, as described in Figure 1.

**Figure 1 F1:**
[figure not shown]
Study flowchart.

### Participants

2.2

#### Inclusion criteria

2.2.1

Patients with spinal or limb fracture will be recruited. Patients with fracture occurred within 3 weeks will be included, and the fracture should be confirmed by X-ray or CT. All patients (1000 patients) will be asked to provide written informed consent.

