### Recruitment

2.3

Participants will be recruited from inpatient or outpatient settings in Sichuan Provincial People's Hospital. We will also recruit patients through advertise posters or local media. Patients who meet the inclusion criteria will be asked to provide written inform consent, and baseline evaluation including basic information collection, measurement of bone metabolic markers, measurement of serum H_2_S will be performed subsequently.

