#### Basic information

2.4.1

Basic information such as patient age, gender, and fracture site will be extracted from the hospital medical record system. We will record the basic information of the included participants, which include age, gender, location of facture, smoking, frequency and mode of exercise, accompanied disease, long-term medication (name of medication, dose, and frequency of administration), and other conditions that related to bone fracture.

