### Planned statistical analysis

2.6

The analysis will be conducted by Statistical Package for the Social Sciences (SPSS) Statistics software, version 19.0 (IBM Corporation, Armonk, NY). Continuous data will be presented as the mean ± standard deviation (

), while categorical data will be presented as raw numbers and frequencies. Kolmogorov-Smirnov and Shapiro-Wilk tests will be used to test whether data distribution is normal. Data with normal distribution will be analyzed by Student *t* test. Non-parametric tests Mann–Whitney *U* test will be used to assess the difference between patients with healed fracture and those without when data distribution is skewed. Logistic regression model will be developed with whether fracture is healed at 9 months as dependent variable, with level of H_2_S as independent variable, and with age, gender, baseline characteristics, and other parameters as covariates. *P* < .05 is considered statistical significance.

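### Time since fracture at the baseline H2S sample can differ by weeks between patients, and the healed-versus-unhealed tests do not adjust for it

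*Protocol article*

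**What the plan says.** All places are in the protocol article.

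- Inclusion criteria (2.2.1): "Patients with fracture occurred within 3 weeks will be included".
- Abstract, Methods: "Patient's serum and urine will be collected at baseline for examination". H2S is then compared between patients healed within 9 months and those unhealed at 9 months.
- Recruitment (2.3): "Participants will be recruited from inpatient or outpatient settings in Sichuan Provincial People's Hospital", and also through posters and local media. After consent comes the baseline evaluation, in which "measurement of serum H_2_S will be performed subsequently".
- Study design (2.1): "These indexes will be measured at specific time points, as described in Figure 1". The figure is not shown.
- Basic information (2.4.1): the listed items name no fracture, surgery or sampling date, but the list ends with an open clause on other fracture-related conditions.
- Planned statistical analysis (2.6): a t test or Mann-Whitney test compares healed and unhealed patients. A logistic model for healing at 9 months has H2S level as independent variable, "with age, gender, baseline characteristics, and other parameters as covariates".

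**The concern.** H2S level is treated as one exposure, yet it can be measured soon after injury in one patient and about three weeks after injury in another. If H2S moves during that period, part of the spread between patients reflects the day of the draw and not the patient. There are two consequences.

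- If sampling day is unrelated to healing, the spread it adds is noise and the association shrinks toward the null.
- If sampling day is related to healing, for example because different recruitment routes bring in different kinds of patient at different times, the association is biased. An apparent H2S effect can then arise where there is none, or a real one can be hidden.

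The study's aim makes the question relevant: "we aimed to investigate the change of serum H_2_S in fracture patients". A study that asks whether H2S changes in fracture patients should not rely on its being constant over the first three weeks.

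**Working it through.** The article gives no figure to reproduce. It states 1000 patients without a derivation and reports no H2S time course. The check is therefore one of design logic, followed by illustrations under stated assumptions.

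**Step 1: what the text fixes.** Entry is open up to 3 weeks (21 days) after fracture, and the sample follows consent. A patient who enrols on day 20 cannot have a day-1 sample, whatever the schedule in Figure 1. The spread in time since fracture at sampling therefore comes from the entry window itself. The t test and Mann-Whitney test in 2.6 contain no covariates, so they cannot remove it.

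**Step 2: dilution of the odds ratio.** Let s be the share of the variance of measured H2S that is due to sampling day, with sampling day unrelated to healing. The log odds ratio per fixed H2S unit is multiplied by about (1 − s). One SD of measured H2S is larger than one timing-free SD by the factor 1/√(1 − s). Per SD of measured H2S, the multiplier is thus (1 − s)/√(1 − s) = √(1 − s). With an assumed true odds ratio of 0.70 per timing-free SD (ln 0.70 = −0.357):

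- s = 10%: exp(−0.357 × 0.949) = 0.71
- s = 25%: exp(−0.357 × 0.866) = 0.73
- s = 50%: exp(−0.357 × 0.707) = 0.78

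**Step 3: the drift these shares imply.** Assume that time since fracture at sampling is uniform on 0 to 21 days (SD = 21/√12 = 6.06 days) and that H2S drifts linearly by b timing-free SDs over 21 days. The added variance is b²/12, so s = (b²/12)/(1 + b²/12). Drifts of 0.5, 1, 2 and 3 SD give shares of 2%, 8%, 25% and 43%. Solving for b gives √(12 × 0.111) = 1.15 SD for a 10% share and √12 = 3.46 SD for a 50% share, so 50% requires a very steep drift.

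**Step 4: power of the unadjusted test.** Assume 1000 patients, 10% unhealed, a true standardised difference of 0.3 and two-sided 5%. Power is 81% without drift, and 80%, 78%, 69% and 58% with drifts of 0.5, 1, 2 and 3 SD.

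**Step 5: false positives when sampling day is related to healing.** Assume no true H2S effect, and a mean sampling day that differs by D days between healed and unhealed patients. The spurious shift is bD/21, and its standard error is √(1 + b²/12) × √(1/100 + 1/900). For b = 1 and D = 2, the shift is 0.095, the standard error 0.110 and their ratio 0.87, which gives a false-positive rate of 14%.

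| Drift over 21 days | D = 0 | D = 2 days | D = 4 days |
|---|---|---|---|
| 0.5 SD | 5% | 7% | 15% |
| 1 SD | 5% | 14% | 41% |
| 2 SD | 5% | 35% | 88% |

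With 5% or 20% unhealed the pattern is the same: for b = 1 and D = 2 the rate is 10% or 21%.

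**The case against.** The strongest reply has three parts.

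- The sampling schedule is in a figure that cannot be read here, so the text cannot be faulted for leaving it out. This stands as far as sampling relative to surgery is concerned. It does not dispose of the point, because no schedule can give a late enrollee an early sample. Only holding early enrollees back to a common late day would equalise time since fracture, and the Recruitment section does not suggest that.
- The covariate list is open-ended and may include time since fracture, and itemising covariates is commonly left to the analysis plan. This also stands: the article does not exclude sampling time, it only does not name it. The stated unadjusted tests remain exposed all the same.
- Two of the three dates are already implied. The 3-week criterion needs the fracture date, and the secondary outcome of time from surgery to healing needs the surgery date. This is correct, and it makes the fix cheaper.

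A reader might go further in several ways that the article does not support. It nowhere says that samples fall on both sides of surgery. Day 0 to 21 is the entry window and not a stated sampling window. The sentence on change in H2S is an aim and not an established time course, and since there is a control group it could also mean fracture versus control. Recruitment through several settings makes a link between sampling day and severity plausible, but nothing in the article establishes one.

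**Conclusion.** The point holds as an inexpensive improvement to the design and analysis. It does not show that the planned result will be wrong. The stated entry window and the post-consent sample build in a difference in time since fracture that can reach weeks, and the stated unadjusted tests ignore it.

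Whether this matters in practice depends on how H2S behaves after fracture, which the article does not report. If timing is unrelated to healing, the harm is dilution only. It is small for drifts up to 1 SD over 21 days (power 81% to 78% in the illustration) and moderate at 2 SD (69%). A reader might take the larger figures of 0.73, 0.77 and 0.84, which come from multiplying the log odds ratio by (1 − s). Those hold only per timing-free SD, which the study cannot observe; per SD of measured H2S they are 0.71, 0.73 and 0.78. The more serious risk is bias, but the false-positive rates above 5% all need both a drift in H2S and a difference in mean sampling day between healed and unhealed patients. Both are assumptions, as are the uniform sampling times, the share unhealed and the true effect.

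**What to change.** 1. Record the date of fracture, of surgery (if any) and of the blood draw for every patient.
2. Pre-specify days from fracture to sample as a covariate in the H2S and bone-marker models, for example as a spline so that a non-linear course is allowed.
3. Make the adjusted model the main healed-versus-unhealed comparison, and keep the t test or Mann-Whitney test as description.
4. Where patients have surgery and Figure 1 does not already fix sampling relative to it, add a three-level term: sampled before surgery, sampled after surgery, no surgery. A yes/no term would be undefined for patients who are not operated on, and the inclusion criteria do not require an operation. Add a sensitivity analysis that leaves out post-operative samples.

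The cost is a few model degrees of freedom and one extra recorded date, that of the blood draw. No extra visit or sample is needed.

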#### Exclusion criteria

2.2.2

Patients with wound infection or serious injury requiring amputation will be excluded. Patients with a predicted survival time of less than 9 months because of other serious illness will also be excluded. Patients with pregnancy, psychological disturbance that affects outcome evaluation, or cognitive impairment will also be excluded.

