## Discussion and practical implications

3

Increasing data suggest that H_2_S plays an essential role in bone metabolism. Our previous study found that overexpressed CSE promoted bone fracture healing through increasing collagen secretion, promoting endochondral ossification, and building a full bridge between fracture sites in rat femur.^[11]^ However, whether endogenous H_2_S has the same effect on patients with fracture is still unclear. Therefore, we design an observational study to investigate the relationship between serum H_2_S concentration and bone fracture healing.

The study is an important and innovative prospective cohort study that will provide insight into influence of H_2_S on fracture healing, which, to the best of our knowledge, is the first study in human. The findings may have important implications for therapeutic strategies targeted at promoting healing of fractures.

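### Fractures through tumour stay eligible unless predicted survival is under 9 months, so tumour-related non-union can confound or dilute the unadjusted healed-versus-unhealed comparison

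*Protocol article*

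**What the plan says.** Section 2.2.1 sets eligibility by site, timing and imaging: "Patients with spinal or limb fracture will be recruited", and "Patients with fracture occurred within 3 weeks will be included, and the fracture should be confirmed by X-ray or CT". The cause of the fracture is not part of the rule. The planned number is 1000 patients.

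Section 2.2.2 gives the exclusions. Two concern the injury: "Patients with wound infection or serious injury requiring amputation will be excluded". One concerns other serious illness and works through prognosis alone: "Patients with a predicted survival time of less than 9 months because of other serious illness will also be excluded". The rest are "Patients with pregnancy, psychological disturbance that affects outcome evaluation, or cognitive impairment will also be excluded". Neither section mentions tumour or pathological fracture.

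The abstract says that serum parameters, H2S above all, will be "compared between patients with fracture healed within 9 months and those with fracture unhealed at 9 months". Section 2.5 classes any fracture not healed beyond 9 months as delayed or non-union, whatever the reason. Section 2.6 compares the two groups by t test or Mann-Whitney U test, and adds a logistic model for healing at 9 months with H2S as the independent variable and age, gender and otherwise unnamed baseline characteristics and parameters as covariates. Section 2.4.1 records accompanying disease, long-term medication and other conditions bearing on the fracture.

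The discussion gives the motive: CSE overexpression promoted healing of the rat femur, and "whether endogenous H_2_S has the same effect on patients with fracture is still unclear".

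**The concern.** The survival rule protects follow-up to the 9-month assessment. It does not select fractures in which ordinary repair is possible. In a fracture through myeloma or a metastasis, the lesion itself may decide whether the bone unites and may change bone turnover markers. Such a patient with an adequate prognosis meets every stated criterion.

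Even if these patients are rare in the cohort, they would be over-represented in the unhealed group, because that group is small and they are more likely to be in it. A difference in β-CTX, and possibly in H2S, could then reflect tumour rather than the biology of fracture repair. If tumour has no bearing on H2S, these patients are unhealed for a reason unrelated to the exposure, and a true H2S difference is blurred.

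**Working it through.** **Eligibility.** Take a vertebral fracture through myeloma, 2 weeks old, confirmed on CT, in a patient with predicted survival above 9 months. Site, timing and imaging satisfy section 2.2.1. If the patient has no wound infection, amputation injury, pregnancy, psychological disturbance or cognitive impairment, nothing in section 2.2.2 applies. The patient is eligible and, if unhealed at 9 months, is counted as unhealed.

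**Inputs.** The article supplies N = 1000, the 9-month split and the 0.05 level (taken as two-sided). It gives no tumour share, healing rate or marker distribution, so every other input below is an assumption and there is no figure of the plan's own to reproduce.

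**Concentration in the unhealed group.** Assume 10% non-union in ordinary fractures, 80% in tumour fractures, and a tumour share of 1% or 3%.

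- 1%: unhealed = 990 × 0.10 + 10 × 0.80 = 99 + 8 = 107; tumour share 8/107 = 7.5%. Healed = 893, with 2 tumour fractures (0.2%).
- 3%: unhealed = 970 × 0.10 + 30 × 0.80 = 97 + 24 = 121; tumour share 24/121 = 19.8%. Healed = 879, with 6 tumour fractures (0.7%).

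**Bone turnover marker.** Assume also that β-CTX in tumour patients is 3 times the usual level (usual = 1) and is unrelated to healing otherwise.

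- 1%: unhealed mean (99 + 8 × 3)/107 = 1.15; healed mean (891 + 2 × 3)/893 = 1.00.
- 3%: unhealed mean (97 + 24 × 3)/121 = 1.40; healed mean (873 + 6 × 3)/879 = 1.01.

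Skewed data go to the Mann-Whitney test under section 2.6, which limits the pull of extreme values. Put every tumour patient at the top of the ranking. Then P(unhealed > healed) = 0.5 + 0.5 × (difference in tumour shares), with standard error √[(N + 1)/(12 × n₁ × n₂)].

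- 1%: 0.5 + 0.5 × (0.0748 − 0.0022) = 0.536; SE = √[1001/(12 × 107 × 893)] = 0.0295; expected z = 0.0363/0.0295 = 1.2.
- 3%: 0.5 + 0.5 × (0.1983 − 0.0068) = 0.596; SE = √[1001/(12 × 121 × 879)] = 0.0280; expected z = 0.0958/0.0280 = 3.4.

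So the rank test would usually miss a 1% share and usually flag a 3% share.

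**H2S, false-positive side.** Assume no true H2S effect, a tumour share of 1% to 10%, non-union of 30% to 60% with tumour and 5% to 10% without, and a tumour shift of s SD in H2S. With p_u and p_h the tumour shares in the unhealed and healed groups:

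- spurious difference d = s × (p_u − p_h), in SD;
- SE = √[(1 + s²p_u(1 − p_u))/n_u + (1 + s²p_h(1 − p_h))/n_h];
- rejection probability = Φ(d/SE − 1.96) + Φ(−d/SE − 1.96).

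One case in full: share 5%, risks 60% and 5%, s = 0.5. Unhealed fraction = 0.05 × 0.60 + 0.95 × 0.05 = 0.0775. p_u = 0.030/0.0775 = 0.387; p_h = 0.020/0.9225 = 0.022. d = 0.5 × 0.365 = 0.183; SE = 0.121; d/SE = 1.50; rejection = 32%.

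| Tumour share | Shift in H2S | Spurious difference (SD) | Rejection at 5% level |
|---|---|---|---|
| any | 0 | 0 | 5% |
| 1% | 0.25 to 1 SD | 0.005 to 0.10 | 5% to 11% |
| 5% | 0.5 SD | 0.05 to 0.18 | 8% to 32% |
| 10% | 0.5 SD | 0.09 to 0.26 | 14% to 70% |

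**H2S, dilution side.** Suppose there is a true difference δ among ordinary fractures and tumour patients have the ordinary average H2S. With 10% ordinary non-union, that average lies 0.1δ from the healed mean. The observed difference is δ × (1 − 0.9p_u − 0.1p_h).

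- 1%: 1 − 0.9 × 0.0748 − 0.1 × 0.0022 = 0.93.
- 3%: 1 − 0.9 × 0.1983 − 0.1 × 0.0068 = 0.82.

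The difference shrinks by about 7% to 18% in these two scenarios.

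**The case against.** The strongest reply is that nothing in the article links tumour to serum H2S, the primary outcome. A reader might infer that tumour-driven non-union will be reported as a relation between H2S and healing. The article does not support that: with no shift in H2S there is no bias, and rejection stays at 5%. The 15% to 40% rise shown above is for β-CTX, a secondary marker, and rests on the assumed threefold level. This stands and limits the point.

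Second, section 2.4.1 records accompanying disease and other conditions related to the fracture, and the logistic model allows for baseline characteristics. Naming tumour as a covariate would protect the H2S coefficient even if every tumour patient were unhealed: only the tumour coefficient would then diverge, and those patients would contribute nothing to the H2S estimate. A reader might infer that adjustment fails when nearly all are unhealed; for the H2S coefficient it does not. What remains is that section 2.6 does not name fracture cause, and that covariates do nothing for the t and Mann-Whitney tests.

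Third, the wound-infection exclusion might be read as a principle of removing local causes of failed union, which tumour fractures would then breach. Section 2.2.2 gives no reason for that exclusion, so this is inference and not a contradiction. Nor does the article confine its question to normal bone; it speaks of fracture patients generally.

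Last, keeping these patients and analysing them explicitly is a defensible alternative to exclusion. That is accepted in the fix.

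**Conclusion.** The point holds as a cheap improvement, not as a demonstrated bias. Sections 2.2.1 and 2.2.2 leave fractures through tumour eligible unless predicted survival is under 9 months, and unhealed ones enter an unadjusted comparison that takes no account of cause. They can confound it, most plausibly for bone turnover markers and for H2S only if tumour alters serum H2S, or they can dilute it.

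The size cannot be read from the article. It runs from negligible, with a tumour share near 1% or no marker shift, to material, with a share of 5% to 10% and a 0.5 SD shift. Those shares, the non-union risks and the shifts are all assumptions. The logistic model is exposed only so far as tumour is left out of its unnamed covariates.

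**What to change.** Add to section 2.2.2 an exclusion of pathological fracture through primary or metastatic tumour, including myeloma, and state that osteoporotic fractures remain eligible. Identify any such patients already enrolled from the baseline record, omit them from the healed-versus-unhealed tests and the logistic model, and list them separately. Because the decision rests on a baseline fact, it does not depend on the healing result.

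If the sponsor prefers to keep them, name tumour fracture as a covariate in the logistic model and repeat the unadjusted tests without these patients.

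The work is small: the diagnostic X-ray or CT and the medical record are already in use. The cost is the loss of at most a few percent of patients (assumed) and a slightly narrower population to which the result applies.
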